**Figure 4 F4:**
[figure not shown]
Conceptual model of primary exposure variable and primary outcome variable. CMD, common mental health disorder; GBS, green-blue spaces.

#### WP2: secondary outcome - SWB

SWB is measured by the Warwick-Edinburgh Mental Well-being Scale (WEMWBS) in the NSW for two survey years (2016/2017 and 2017/2018) for a representative population.^67^ The WEMWBS is comprehensive (incorporating elements of both SWB and psychological well-being), short enough to be used in population-level surveys, responsive to change and has been validated among community samples of adults in the UK.^68^ WEMWBS scores are on continuous scale from 14 to 70.

#### WP1: secondary outcome - GP events

We have the total number of events recorded for each person in a WLGP dataset. We will calculate the number of GP events, converting to a binary daily activity or no activity aggregated to quarterly counts. This eliminates double counting (eg, counting the return of large quantities of test results only once). These are purposefully all events rather than those related only to CMD because this will capture people who frequently visit their GP but for whom no CMD diagnosis has been made. This will allow us to explore social isolation and as indicator of undiagnosed CMD.

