### Health datasets

#### Welsh Longitudinal General Practice

The Welsh Longitudinal General Practice (WLGP) dataset contains individual-level health data including Read codes^64^ for all diagnoses, symptoms and treatments recorded by a GP and we will extract outcome data for each person from 2008 to 2018.

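### GP event days count any recorded activity, so they mix visits with treatment and monitoring and are not a specific measure of frequent visiting, isolation or undiagnosed CMD

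*Protocol article*

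**What the plan says.** In the protocol article, the section on the WP1 secondary outcome of GP events starts from every entry in the record: "We have the total number of events recorded for each person in a WLGP dataset". The construction follows: "We will calculate the number of GP events, converting to a binary daily activity or no activity aggregated to quarterly counts". The stated benefit is that same-day duplicates disappear, with the example of "counting the return of large quantities of test results only once".

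The same section gives the reason for not restricting the events: "These are purposefully all events rather than those related only to CMD because this will capture people who frequently visit their GP". The people it has in mind are those without a CMD diagnosis, and the count is offered as a way to explore social isolation and as an indicator of undiagnosed CMD.

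The section on the Welsh Longitudinal General Practice dataset describes its content as codes "for all diagnoses, symptoms and treatments recorded by a GP". Table 2 of the Analysis plan lists the outcome as a count of GP event days, with gender, age and comorbidities as individual-level confounders and deprivation and settlement type at area level. The model levels are area, individual and quarter.

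**The concern.** The rationale speaks of visits, but the definition counts record entries. A day on which results come back is not a visit, and a day with a treatment record need not be one. A person under routine treatment and monitoring for a physical condition can therefore look like a frequent attender, and a person who attends a few times with little else on file can look like an infrequent one.

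What is at stake is interpretation. The Introduction names physical activity as one route from green-blue spaces (GBS) to health. If GBS changes physical illness, treatment and monitoring days may change with it. An association between GBS and event days could then reflect physical-health care, while the rationale invites a reading in terms of contact-seeking, isolation or hidden CMD.

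**Working it through.** The article states no event rate, share of event days by type, or sample size for this outcome, so there is no figure to reproduce. The check sets the sections side by side and adds a labelled illustration.

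**Step 1. What makes an active day.** The GP events section takes all entries in the dataset and applies no filter by type. Test-result returns are named as something that counts once per day. Treatment records come in by inference, since the dataset section lists treatments among its contents. The article does not mention prescriptions or issue dates as such. Visits that produce a diagnosis, symptom or treatment code also count.

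**Step 2. What the deliberate choice covers.** The stated choice is "These are purposefully all events rather than those related only to CMD". That settles CMD against non-CMD events. It does not address visits against non-visit entries, so the mismatch is not something the article has considered and accepted.

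**Step 3. What the once-per-day rule does.** It collapses several entries on one day to one. It does nothing across days: one consultation plus its result filed on a later day gives 1 + 1 = 2 event days for a single visit.

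**Step 4. What adjustment does.** Comorbidities in Table 2 should absorb part of the difference in illness between people. They cannot turn a results day into a visit. They do not separate two people with the same condition who have different treatment or monitoring intervals, and they need not capture a change within one person when treatment or monitoring starts or changes. Practice is not a model level, so differences in recording between practices are not modelled directly.

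**Step 5. Overlap with the primary outcome.** CMD treatment days come from the same GP records, and the article states no restriction of event days to people without a CMD diagnosis. Among CMD cases, those treatment days would therefore add to this secondary outcome as well.

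**Step 6. Illustration.** All intervals here are assumptions; none is in the document. The quarter is taken as 91 days, and treatment records are assumed not to coincide with a visit.

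Event days without a visit = 91 / interval between treatment records.

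- Every 28 days: 91/28 = 3.25, about 3.3
- Every 56 days: 91/56 = 1.625, about 1.6
- Every 84 days: 91/84 = 1.08, about 1.1
- Two treatments recorded on different days, each every 28 days: 2 × 3.25 = 6.5
- One results day per quarter added to the first three: 4.25, 2.625 and 2.08

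A person who visits twice and has no other record scores 2. Against the single-treatment scores of 3.25, 1.625 and 1.08, the ranking by event days reverses the ranking by visits at 28 days, but not at 56 or 84. With the results day added, it reverses at all three. Starting a treatment recorded every 28 days would also raise a person's own count by 3.25 per quarter with no change in visiting.

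**The case against.** The strongest case for the plan has four parts.

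1. *The breadth is deliberate and the wording modest.* The variable is called GP event days, not visits; it is secondary; and the article speaks only of exploring and indicating. This is fair. Nothing in the document says that an association will be reported as isolation or hidden CMD. It does, however, give frequent visiting as the reason for the definition, and the definition does not isolate it.

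2. *Steady background treatment adds a roughly constant amount to a person's count.* The individual level of the model, the confounders and the use of change in GBS access and exposure all help. No reason is given why treatment intervals or practice policy should vary with GBS after adjustment. This stands in part: bias from those sources is not shown, and some of the effect may be noise. It does not answer the case where GBS affects physical illness, nor change within a person when care starts or changes.

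3. *Code lists belong to the full protocol or analysis plan.* True, and their absence is not the point. The point is a definition and a rationale, both stated here, that do not fit each other.

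4. *A visit-based count may be hard to build.* The document mentions no consultation marker, and a real visit may leave only a treatment code. This stands, and it is why replacing the outcome outright is not advised.

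A reader might go further and infer that the outcome fails to capture visits, or that it mainly measures background treatment of long-term illness. The document supports neither. Recorded visits count, the mix is not given, and the intervals in the illustration are assumed.

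**Conclusion.** The concern holds in a limited form. GP event days measure total recorded primary-care activity, in which visits are mixed with treatment and monitoring of any illness. They are not a specific measure of frequent visiting, social isolation or undiagnosed CMD, and an association with GBS could reflect physical-health care. Comorbidity adjustment reduces this only in part.

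The size is unknown, because the share of event days without a visit is not in the document. The illustration shows that rankings can reverse under plausible assumptions; it does not show that they usually do, or that a GBS estimate is biased in a given direction. The inclusion of test results is explicit. The inclusion of treatment records rests on reading all events together with the dataset description. The matter affects a secondary outcome and what may be concluded from it; it does not invalidate the all-event count as a measure of overall activity.

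**What to change.** - Keep the all-event day count and describe it as total recorded primary-care activity.
- Add a second quarterly count from the same data that leaves out days whose only codes are test results, treatment issue or administration.
- Tie any statement about visiting, isolation or undiagnosed CMD to the second count, and report both counts side by side with the same model and confounders.
- State that the second count is closer to visits but is not a pure visit count.

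The cost is a code list fixed before analysis and a further model run on records the study already plans to use. The downside is that some true visits carry only a treatment code and would be dropped, and coding habits may differ between practices. Comparing the two counts makes this visible: if the GBS estimates agree, the interpretation is firmer; if they differ, the all-event result should not be read as a result about visiting. If a second count proves impracticable, the minimum is to relabel the outcome and withdraw the visit-based rationale.

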### Participants

Our study population contains people aged 16 years and older living in Wales, UK. WP1 includes the total adult population registered with a general practitioner (GP), providing GP records to SAIL. This is expected to be about 1.7 million adults in Wales (see figure 2). WP2 includes a representative sample of the adult population in Wales based on the NSW for 2 years (cross-sectional samples in 2016/2017 and 2017/2018). The NSW has an annual sample of approximately 12 000 responders and GBS visit questions are asked of 50% of that sample. This provides a total cross-sectional sample of 12 000 (over the 2 years) for this part of the study.

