## Statistical analysis

### Outcome variables

#### WP1 and 2: primary outcome - CMD

Change in counts of CMD treatments for adults identified as CMD cases within the corresponding time periods for the 70% of adults in Wales for whom we have GP data records in SAIL (1.7M adults). Prevalence algorithms,^65 66^ detect cases of CMD (anxiety and depression) from routinely collected GP data. We will use the algorithm that incorporates: an historical diagnosis and currently treated, with current diagnosis whether treated or untreated, to identify CMD cases. For each adult, and for the time periods (quarters) identified as a CMD case, treatments will be counted per day and aggregated into quarterly counts. Figure 4 shows a conceptual model of exposure variable (GBS access and exposure) and primary outcome variable (CMD treatments).

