### Analysis plan

We will provide descriptive statistics of GBS access and exposure and changes in GBS access and exposure by household, Lower Layer Super Output Area (LSOA), deprivation quintiles using Welsh Index of Multiple Deprivation (WIMD) and population characteristics. NSW data will have descriptive statistics of each of the survey questions we will use (number of visits, labour market status, etc).

Across both WPs, we have outcomes of two distinct types: continuous (SWB) and counts (CMD treatments and GP event days). We intend to analyse the continuous outcome using a linear model. Poisson models will be used to analyse the longitudinal count data.

Our data are hierarchical in nature: WP1: three-level data: LSOA/Individual/Time (Quarter); WP2: two-level data: LSOA/Individual. Accordingly, we will adopt a multilevel modelling approach. We will generalise the standard linear and Poisson models to handle two or three levels of variation, as appropriate. The resulting two-level and three-level models will allow us to estimate the extent to which variation at each level may be explained by confounding variables (see table 2). Having controlled for confounders, we will proceed to add access and exposure variables to our models, thereby allowing us to test for the significance of the access and exposure variables in the presence of the confounders. Inclusion of these variables in the above models will permit us to estimate their direct effects on our outcomes. Having included the main effects of both confounders and access and exposure variables, we will proceed to test for the significance of selected pairwise interactions of interest, as shown in table 2.

**Table 2 T2:** Analysis summary (P: primary; S: secondary)

WP	Outcomes (type)	Exposures	Confounders	Interactions of interest
1	P: CMD (count)	P: Access and exposure to GBS.	LSOA level: Quintile of deprivation (WIMD). Category of urban/rural settlement type (ONS classification).	Change in access and exposure to GBS by deprivation.
	S: GP event days (count)	S: Time of move(s).	Individual level (SAIL): gender, age, comorbidities.	Change in access and exposure to GBS by time of move(s).
2	P2: SWB (continuous)	P2: Access and exposure to GBS.	LSOA level: as per WP1.	Exact number of visits by individual level deprivation.

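### GP event days are meant to serve as an indicator of undiagnosed CMD, but the count and its model pool diagnosed and undiagnosed adults, so known cases may supply part of any association

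*Protocol article*

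**What the plan says.** The section on GP events in the Protocol article starts from all recorded activity: "We have the total number of events recorded for each person in a WLGP dataset". Each day is reduced to active or inactive and the active days are summed by quarter. All event types are kept on purpose ("These are purposefully all events rather than those related only to CMD"), on the ground that "this will capture people who frequently visit their GP but for whom no CMD diagnosis has been made". The intended use follows: "This will allow us to explore social isolation and as indicator of undiagnosed CMD".

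The population is not narrowed to match. Under Participants, "WP1 includes the total adult population registered with a general practitioner (GP), providing GP records to SAIL", about 1.7 million people. In Table 2 (Analysis plan), GP event days are a secondary count outcome for WP1. The confounders are area deprivation, settlement type and "Individual level (SAIL): gender, age, comorbidities". The interactions are with deprivation and with time of move. CMD status is not listed as a restriction, stratum or interaction.

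For the primary outcome, an algorithm applied to the GP data identifies CMD cases by quarter, and for those cases "treatments will be counted per day and aggregated into quarterly counts". The Health datasets section says that these GP records hold codes for diagnoses, symptoms and treatments. Stratifying by CMD is mentioned once, in the WP2 objectives, as something to be considered as a check on reverse causation.

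**The concern.** The reason given answers one question, which is why events unrelated to CMD should count. It leaves open whose events should count. The group of interest is defined by having no diagnosis, yet adults with a diagnosis are in the count.

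The overlap with the primary outcome follows from the definitions. A day with a recorded CMD treatment is also a day with GP activity, so a fall in treatment days among known cases can lower both outcomes. If the all-adult GBS coefficient is then taken as evidence on undiagnosed CMD, it may partly repeat the primary result. At stake is the interpretation of one secondary outcome. The primary outcome is not affected.

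**Working it through.** The article states no event-day rate, diagnosed prevalence, effect size or power for this outcome, so there is no figure to reproduce. What follows shows possible size only, and every rate below is an assumption.

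**Mechanism A: better GBS lowers the share of case-quarters, and non-case event rates do not change.** Let p be the share of person-quarters that are case-quarters, and r the event-day rate in cases relative to non-cases. The mean, in units of the non-case rate, is m = (1 − p) + p·r. The pooled rate ratio (RR) is m after the reduction divided by m before it. Averted case-quarters are assumed to attend at the non-case rate.

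| p | r | Reduction in p | Cases' share of event days, p·r/m | m before | m after | Pooled RR |
|---|---|---|---|---|---|---|
| 0.05 | 1.5 | 5% | 0.075/1.025 = 7% | 1.025 | 1.02375 | 0.999 |
| 0.10 | 3 | 10% | 0.30/1.20 = 25% | 1.20 | 1.18 | 0.983 |
| 0.20 | 3 | 10% | 0.60/1.40 = 43% | 1.40 | 1.36 | 0.971 |

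Precision for the middle row, assuming two equal groups of 850,000 (half of 1.7 million), one event day per quarter in non-cases, 44 quarters (11 years × 4) and a between-person frailty variance of 1:

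- SE(log RR) = √[2(1.2² + 1.2/44)/850,000] / 1.2 = 0.00155.
- |z| = |ln 0.983| / 0.00155, about 11.
- This ignores clustering by LSOA. With variance inflated tenfold, |z| is about 11/√10 = 3.4.
- In the smallest row |z| is about 0.8, even without inflation.

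**Mechanism B: diagnosed adults have fewer event days, and undiagnosed adults do not change.** Let k be the event-day rate in diagnosed relative to undiagnosed adults. The diagnosed share of event days is s = p·k/(p·k + 1 − p), and the pooled RR is s·RR(diagnosed) + (1 − s)·1. Take p from 0.10 to 0.25. The upper value borrows the one-in-four UK figure in the Introduction, which is not a GP-diagnosed prevalence. Take k from 1 to 3.

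- s runs from 0.10 (p = 0.10, k = 1) to 0.75/1.50 = 0.50 (p = 0.25, k = 3).
- With RR 0.95 in diagnosed adults, the pooled RR is 0.995 to 0.975.
- With RR 0.90 in diagnosed adults, the pooled RR is 0.990 to 0.950.
- For RR 0.95, one quarter of data and 1 to 3 event days per quarter in undiagnosed adults, |z| is 3.3 to 34.8 under pure Poisson variance and 1.0 to 11.0 with tenfold overdispersion. The latter exceeds 1.96 in most scenarios, but not all.

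**What a split would do.** Under B, the undiagnosed stratum returns RR 1.00, as it should. Under A, a stratum of current non-cases updated each quarter has a problem of its own, because the averted case-quarters move into it. With p falling from 0.10 to 0.09, and those adults still attending at k times the non-case rate, the stratum shows RR = (0.90 + 0.01k)/0.91. This is 1.005 at k = 1.5 and 1.022 at k = 3, from composition alone. Strata fixed before follow-up reduce this, because later exposure cannot move anyone between them.

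**The case against.** The strongest reply is that the article claims less than a reader may take from it. It says that the count will capture undiagnosed attenders, which means include them, and it speaks of exploring and of an indicator. It does not say that the count isolates undiagnosed CMD, and it sets no rule for interpreting the coefficient. As a reason for counting all event types the sentence is sound, and the all-adult count is a valid measure of overall GP use. An analysis plan that is not shown may split by case status, and comorbidities may include CMD.

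Much of this stands. A reader might infer that the outcome cannot answer its question at all, or that any signal would come entirely from diagnosed cases. The document supports neither. The wording is exploratory, the inputs above are assumed, and at the low end the effect would not be detectable.

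A reader might also infer that an analysis limited to current non-cases settles the matter. It does not, given the opposite artefact of similar size shown above. Even among non-cases, physical illness drives GP contact.

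The pairing of measure and purpose remains. The article itself states the outcome, its intended reading and its model, so the point does not rest on an omitted detail. If comorbidities did include CMD, adjustment would still give a single pooled exposure effect, not the effect in undiagnosed adults. The stratification mentioned under WP2 is tentative and serves another purpose.

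**Conclusion.** The point holds in a limited form. As described, the all-adult estimate mixes known cases with the group that the outcome is meant to indicate, so an unknown part of any GBS association may come from known cases.

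Under mechanism A the pooled RR is about 0.97 to 0.999 with non-case event rates unchanged. Under mechanism B it is 0.95 to 0.995. These ranges rest on assumed case shares, relative event rates and GBS effects, and the z values ignore LSOA clustering. They show that such a signal is plausible in a cohort of this size, not that it will occur. The matter deserves correction, at moderate weight, because it touches one secondary outcome read in an exploratory way.

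**What to change.** - Keep the all-adult model and describe it as a measure of overall GP use.
- Fit the same model by CMD history fixed at cohort entry, or before the exposure change, using the primary-outcome algorithm on the GP records. Adults with no CMD history form one stratum and those with a history the other.
- Add a sensitivity analysis restricted to person-quarters with no CMD recorded to date. The two approaches have different weaknesses. The fixed stratum comes to include adults diagnosed later, while the updated one is selected on something GBS may affect.
- Base any reading about undiagnosed CMD on the no-history stratum, reported beside the all-adult result. State that later diagnosis may itself be affected by GBS and that all-cause contact is non-specific. Otherwise drop that reading.

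The cost is one extra stratified model and its sensitivity analysis, built on an algorithm already planned for the primary outcome. No new data are needed. Some residual selection remains.

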#### WP2: secondary outcome - Office for National Statistics SWB

We will have individual responses in NSW to the four standard SWB questions (life satisfaction, sense of worth of activities, happiness, and anxiety) as used by Office for National Statistics and the Organisation for Economic Co-operation and Development.^69^ As well as being relatable to national representative survey data, these data have also been used in previous GBS visit research using the comparable Monitor of Engagement with the Natural Environment for England.^45^

### Analysis plan

We will provide descriptive statistics of GBS access and exposure and changes in GBS access and exposure by household, Lower Layer Super Output Area (LSOA), deprivation quintiles using Welsh Index of Multiple Deprivation (WIMD) and population characteristics. NSW data will have descriptive statistics of each of the survey questions we will use (number of visits, labour market status, etc).

Across both WPs, we have outcomes of two distinct types: continuous (SWB) and counts (CMD treatments and GP event days). We intend to analyse the continuous outcome using a linear model. Poisson models will be used to analyse the longitudinal count data.

Our data are hierarchical in nature: WP1: three-level data: LSOA/Individual/Time (Quarter); WP2: two-level data: LSOA/Individual. Accordingly, we will adopt a multilevel modelling approach. We will generalise the standard linear and Poisson models to handle two or three levels of variation, as appropriate. The resulting two-level and three-level models will allow us to estimate the extent to which variation at each level may be explained by confounding variables (see table 2). Having controlled for confounders, we will proceed to add access and exposure variables to our models, thereby allowing us to test for the significance of the access and exposure variables in the presence of the confounders. Inclusion of these variables in the above models will permit us to estimate their direct effects on our outcomes. Having included the main effects of both confounders and access and exposure variables, we will proceed to test for the significance of selected pairwise interactions of interest, as shown in table 2.

**Table 2 T2:** Analysis summary (P: primary; S: secondary)

WP	Outcomes (type)	Exposures	Confounders	Interactions of interest
1	P: CMD (count)	P: Access and exposure to GBS.	LSOA level: Quintile of deprivation (WIMD). Category of urban/rural settlement type (ONS classification).	Change in access and exposure to GBS by deprivation.
	S: GP event days (count)	S: Time of move(s).	Individual level (SAIL): gender, age, comorbidities.	Change in access and exposure to GBS by time of move(s).
2	P2: SWB (continuous)	P2: Access and exposure to GBS.	LSOA level: as per WP1.	Exact number of visits by individual level deprivation.
	P1: CMD (count)	S: Level of engagement in 150+ min of moderate or vigorous intensity activity per week.	Individual level and NSW: gender, age, comorbidities, highest educational qualification, marital status (incl. living with partner).	Exact number of visits by residential GBS.
			Exact number of visits made outdoors for recreation in last 4 weeks.	

CMD, common mental health disorder; GBS, green-blue spaces; GP, general practitioner; NSW, National Survey for Wales; ONS, Office for National Statistics; SAIL, Secure Anonymised Information Linkage; SWB, subjective well-being; WP1, work package 1.

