### Aim

Our primary aim is to quantify the impact of changes in access to GBS and ambient GBS exposure on CMD and SWB, for a national population. This will be fulfilled through a number of objectives within two work packages (WPs). WP1 will use routinely collected health and demographic data (data collected for purposes other than research^48^) stored in an anonymised databank to examine the risk of CMD using longitudinal changes in access to neighbourhood GBS. WP2 will link routine data in the anonymised databank with in-depth survey responses from the data linked National Survey for Wales (NSW) to evaluate a representative sample of Welsh residents’ self-reported well-being and GBS use.

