### Objectives

#### WP1

Create a longitudinal dataset of GBS in Wales using UK Ordnance Survey (OS), local authority and remotely sensed satellite data.Create longitudinal, residential GBS accessibility indices for all homes in Wales using the longitudinal GBS dataset in a Geographic Information System (GIS).Create an 11-year dynamic cohort of individual-level longitudinal residential GBS accessibility indices to answer the research question(s): ‘Do people with different GBS access through time have different associated risks of having a CMD?’ and ‘Is the association between changes in access and exposure to GBS and CMD modified by multiple sociophysical variables, migration and socioeconomic disadvantage?’

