## Methods and analysis

### Design

The GBS project is a retrospective and controlled, population-wide study. We will evaluate the association between changes in access and exposure to GBS, on the risk of CMD (WP1) and SWB (WP2). This could be either at environment level (eg, a change in the GBS itself) or person level (eg, moving home, better access to transport). WP1 will use longitudinal data to examine variability in time and space of access and exposure to GBS and examine whether this could be due to planning and environmental policies. WP2 will use cross-sectional data to investigate whether visits to GBS improve SWB.

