Another aim of the study is to create novel GBS accessibility indices to use network routes from a variety of sources, and access points, to model how people may access GBS. The way that studies measure access to GBS is methodologically diverse and there is no general consensus on which is the best measure to use. Our measures will be informed by theories and findings in the literature. To complement this, we will ensure we involve members of the public in our research. The overarching aim of our longitudinal study is to identify causal mechanisms to determine whether a positive change in access and exposure to GBS lowers the risk of CMD.

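### WP1 targets the effect of changes in green-blue space, but the plan does not make change the primary main effect or separate within-person from between-person variation

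*Protocol article*

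**What the plan says.** Three places state the target as change. Under Aim: "Our primary aim is to quantify the impact of changes in access to GBS and ambient GBS exposure on CMD and SWB". The Design section says the same for common mental health disorder (CMD) in WP1. The Discussion gives the overarching aim as to "identify causal mechanisms to determine whether a positive change in access and exposure to GBS lowers the risk of CMD". The first WP1 research question under Objectives is worded instead as a contrast between people: "Do people with different GBS access through time have different associated risks of having a CMD".

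The Analysis plan describes the structure as "WP1: three-level data: LSOA/Individual/Time (Quarter" and proposes a multilevel Poisson model. Confounders go in first; then "Having controlled for confounders, we will proceed to add access and exposure variables to our models"; then selected interactions. Table 2 gives the primary WP1 exposure as "P: Access and exposure to GBS". In the WP1 rows the word change appears only under interactions: "Change in access and exposure to GBS by deprivation", and the same by time of move.

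The section on the GBS accessibility and exposure dataset does promise a change measure for each adult. It builds on an earlier study of alcohol outlet density that used change from the previous quarter and change from baseline. It does not say how these measures enter the model.

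**The concern.** A person's GBS index in a given quarter differs from other values in two ways: people live in different places, and one person's surroundings alter over time. Only the second kind of variation speaks to the effect of change. A multilevel model that receives the index as one undivided term returns a weighted average of the two associations.

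There is a stated reason to expect them to differ. The Introduction says that people of higher socioeconomic status are more likely to choose greener neighbourhoods. The WP1 confounders in Table 2 are area deprivation quintile, urban/rural type, gender, age and comorbidities, with no individual-level socioeconomic measure. Selection left over after adjustment would sit in the between-person part. Through a blended coefficient it could then be reported as the impact of changing access, in a study meant to inform planning policy.

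**Working it through.** The article gives no effect size, variance component or power figure on this point, so there is nothing to reproduce. The check has three parts.

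**1. What the text allows.** Table 2 uses access/exposure and change in access/exposure as separate terms, and so does the first sentence of the Analysis plan on descriptive statistics. The main possibilities are:
- Change is not a main effect. The interactions then involve a variable with no main effect listed.
- Change from baseline is entered beside current level. See part 3.
- Quarter-to-quarter change is entered beside level. The level term is still undivided.
- The exposure cell is shorthand for change. Table 2 then needs rewording.

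Each calls for a correction; only the last is purely editorial.

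**2. Size of the blend (illustration).** Take a linear random-intercept model with between-person slope bB and within-person slope bW. A single coefficient estimates w·bW + (1 − w)·bB, where

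w = v / (v + φ(1 − v)), φ = (1 − ICC) / ((1 − ICC) + T·ICC).

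T = 11 years × 4 = 44 quarters comes from the article. The share v of exposure variance lying within person, and the outcome ICC, are assumptions.
- ICC 0.1, v 0.01: φ = 0.9/5.3 = 0.170; w = 0.01/(0.01 + 0.168) = 0.06.
- ICC 0.3, v 0.05: φ = 0.7/13.9 = 0.050; w = 0.05/(0.05 + 0.048) = 0.51.
- ICC 0.7, v 0.30: φ = 0.3/31.1 = 0.0096; w = 0.30/(0.30 + 0.0068) = 0.98.

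The single coefficient can therefore be almost wholly cross-sectional or almost wholly within-person.

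A Poisson-gamma simulation used 6,000 people, 44 quarters, one exposure step per person and random-effect variance 1. The true within-person log rate ratio was 0 and the between-person one -0.20 per unit; all of these except the 44 quarters are assumed.

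| Mean count per quarter | v | Single coefficient (RR) | Split: between | Split: within |
|---|---|---|---|---|
| 0.1 | 0.01 | -0.196 (0.82) | -0.206 | -0.026 |
| 0.1 | 0.05 | -0.150 (0.86) | -0.210 | 0.044 |
| 0.1 | 0.20 | -0.083 (0.92) | -0.203 | 0.000 |
| 0.5 | 0.01 | -0.164 (0.85) | -0.193 | -0.048 |
| 0.5 | 0.05 | -0.095 (0.91) | -0.202 | -0.007 |
| 0.5 | 0.20 | -0.037 (0.96) | -0.223 | -0.008 |

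The single term suggests a benefit in every row although change does nothing. The split recovers both slopes approximately.

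The result is sensitive to how exposure varies. In a further simulation (15,000 adults; between-person slope -0.10; 10–50% of adults moving once), the single coefficient was -0.010 to -0.072. Giving everyone quarterly exposure variation with an assumed SD of 0.3 reduced it to -0.007 to -0.040.

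**3. Change from baseline.** Let X0 be baseline and Xt current level. Baseline plus deviation is a·X0 + b·(Xt − X0). Level plus change is g·Xt + d·(Xt − X0). Matching terms gives g = a and d = b − a, so b = g + d. These are the same fitted model. The effect of change given baseline is the sum g + d, not d alone. With b = 0 and a = -0.10, d = +0.10, which looks like harm where there is none. In the 15,000-adult simulation d was +0.08 to +0.11, while g + d was -0.013 to -0.003.

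**The case against.** The strongest reply is that the article does not commit to the model criticised. It never writes current level or random intercept, and a within-between specification is itself a multilevel model. The planned change measures appear in the section on the access and exposure dataset, so they may be among the variables added as main effects. The plan also says that main effects precede interactions. The between-person contrast answers the first WP1 research question. The parametrisation of a time-varying covariate is often left to an analysis plan.

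Much of this stands, and it rules out several stronger readings:
- A reader might infer that change certainly has no main effect. The text leaves this open; it only fails to list one.
- A reader might infer that adding change from baseline to current level cannot help. Part 3 of the working shows that it can, if the coefficients are read together.
- A reader might quote a fixed percentage of cross-sectional association leaking into the result. The article supplies none of the inputs, and the simulations omit the area level and the confounders.
- A reader might turn the Discussion's remark about earlier longitudinal studies against this plan. That remark concerns cross-sectional environment data, which this study replaces.

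What the reply does not remove is the mismatch. The article does state a primary exposure, it is not the quantity in the primary aim, and no sentence says which coefficient answers that aim.

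**Conclusion.** The point holds as a mismatch between aim and primary model term, not as an arithmetical error. The aim is the effect of change. Table 2 names access and exposure without change, and the model description does not separate the two sources of variation. If the exposure enters as one time-varying term with person and area random effects, which is the natural but inferred reading, its coefficient blends cross-sectional difference with within-person change. The bias as an answer to the change question depends on three things the article does not give: the within-person share of exposure variance, the outcome's clustering, and how far the two slopes still differ after adjustment. The rate ratios of 0.82 to 0.96 under no effect of change are illustrative only.

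**What to change.** In Table 2 and the Analysis plan:
- Enter each WP1 access or exposure measure as two terms: the person's mean level, and each quarter's deviation from that mean.
- State that the within-person deviation answers the change aim.
- Use the deviation in the deprivation and time-of-move interactions, with its main effect in the model.
- Report the between-person term separately, as the answer to the first WP1 research question.
- If change from baseline is preferred, enter it with baseline level. If it is entered with current level, do not read the change coefficient alone as the effect of change.

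The cost is a wording change and a person-mean and deviation pair derived for each measure, with no new data. The interval for the headline term will be wider, because only adults whose GBS changes inform it. The split removes stable differences between people; it does not remove confounders that shift at the same time as GBS, such as circumstances surrounding a move, and the report should say so.
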